### Data analysis

Analyses for Hypotheses 1 and 2, comparing outcomes between groups, will employ mixed effects repeated measures models that use all available data for each participant. Separate analyses will be conducted for each primary outcome variable. This same analytic approach, with the addition of interaction terms, will be used for secondary analyses examining moderators (e.g., extent of use, gender). Missing data will be handled using a maximum likelihood approach to estimate covariances, variances and means.

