**Methods:**

Potential participants will be screened using an online survey to identify participants meeting criteria for problem gambling. As part of the baseline screening process, measures of current depression and anxiety will be assessed. Eligible participants agreeing (*N* = 280) to take part in the study will be randomized to one of two versions of an online intervention for gamblers – an intervention that just targets gambling issues (G-only) versus a website that contains interventions for depression and anxiety in addition to an intervention for gamblers (G + MH). It is predicted that problem gamblers who do not have co-occurring mental health symptoms will display no significant difference between intervention conditions at a six-month follow-up. However, for those with co-occurring mental health symptoms, it is predicted that participants receiving access to the G + MH website will display significantly reduced gambling outcomes at six-month follow-up as compared to those provided with G-only website.

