## Major research questions

The proposed trial will compare two Internet intervention websites – an intervention that just targets gambling issues (G-only) versus one that contains interventions for anxiety and depression in addition to an intervention for gamblers (G + MH). The primary hypotheses are:**Hypothesis 1:** For problem gamblers with co-occurring mental health symptoms, it is predicted that participants provided access to the G + MH website will display significantly reduced gambling outcomes at three- and six-month follow-ups as compared to those provided access to the G-only website.**Hypothesis 2:** Problem gamblers without co-occurring mental health symptoms will display no significant difference between the G-only and G + MH websites at three- and six-month follow-ups.**Hypothesis 3:** Respondents who have more involvement with the G-only intervention between baseline and three-month follow-up will demonstrate more improvement in gambling outcomes at six-month follow-up, compared to respondents who have less involvement with the G-only intervention.

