### Follow-up assessments

Three and six months after randomization, an email invitation will be sent to participants containing a link to the follow-up assessment. Up to two reminder emails will be sent to promote retention in the trial. The follow-up will consist of an assessment of gambling behaviour, problem gambling severity (NODS), self-rated improvement, psychiatric distress, alcohol and illicit drug use, quality of life, and use of other treatment resources. Primary outcome measures will consist of problem gambling severity (as measured by the NORC DSM-IV screen for Gambling Problems (NODS – past 3-month version) [41], and mean days per month gambling in the past 3 months.

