### Power analysis

We propose to collect a sample of 280 participants and we estimate that we will successfully follow about 224 participants at six months (20 % attrition) [34]. This number will also provide sufficient power to conduct the proposed statistical tests comparing hypotheses, based upon gambling frequency and NODS data from Hodgins et al. [33, 34], assuming a correlation of .5 between baseline and follow-up values, power = .80 and an α = .05. This sample size will be sufficient to detect a difference of about two gambling days per month between conditions at each follow-up interval. Smaller differences may not be clinically important. Similarly, this sample size will be sufficiently powered to detect a 1 point difference on the NODS at six months. These calculations are based upon a repeated measures ANOVA model. The proposed analyses will employ mixed effects repeated measures models and, as such, will have greater statistical power because all observed data are included.

Also important is to ensure that there are enough females in the sample to conduct the proposed sex difference analyses. Approximately a third of problem gamblers in the general population are female [47]. With the assumption that this proportion would be maintained in our sample (i.e., those who would be concerned about their gambling and agree to participate in the study), roughly 92 of the 280 respondents will be female. A sample with 23 respondents per condition is sufficiently large to conduct the proposed analyses. However, our experience using these same recruitment methods in other studies is that females tend to be more interested in self-help materials than males and also, to be willing to participate in the proposed research. Thus, we fully anticipate that more than a third of respondents will be female (perhaps as many as half will be female if the recruitment trends in our other studies hold true with this trial as well).

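### Hypothesis 1 is tied to different time points in different places, and two unranked primary outcomes share one unsplit alpha, so what would confirm it is not fixed

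*Protocol article*

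**What the plan says.** **Outcomes.** Follow-up assessments states: "Primary outcome measures will consist of problem gambling severity", measured by the three-month NODS, "and mean days per month gambling in the past 3 months". Neither outcome is ranked above the other.

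**Analysis.** Under Data analysis, the comparisons for Hypotheses 1 and 2 "will employ mixed effects repeated measures models that use all available data for each participant", and "Separate analyses will be conducted for each primary outcome variable". The text does not say whether each model yields one overall treatment test or a test at each visit.

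**Alpha.** The only figure is in Power analysis: "power = .80 and an α = .05". It is not divided or ordered between the outcomes.

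**Time point.** Three places differ:
- Abstract, Methods: among those with co-occurring symptoms, "participants receiving access to the G + MH website will display significantly reduced gambling outcomes at six-month follow-up".
- Major research questions, Hypothesis 1: the G + MH group "will display significantly reduced gambling outcomes at three- and six-month follow-ups as compared to those provided access to the G-only website".
- Power analysis: the two-day difference in gambling days is claimed for both follow-ups, the one-point NODS difference for six months only.

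**The concern.** Hypothesis 1 carries the trial's main claim. Two outcomes and two visits give up to four group comparisons, and the article describes the relevant visits in three ways. An analysis plan written later cannot agree with all three. A reader of the results could not tell from this article whether a three-month finding on one outcome was a pre-specified confirmation or a selected one. At stake are the false-positive rate for the main hypothesis and the meaning of the stated power. Both depend on a success rule that the text leaves open.

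**Working it through.** **1. The plan's own figure.** 280 × (1 − 0.20) = 224, so the attrition arithmetic is right. The power claim cannot be reproduced because no standard deviation is given. With 224/2 = 112 per arm, two-sided alpha .05 (sidedness is not stated, so this is assumed) and power .80, the detectable difference is (1.960 + 0.842) × √(2/112) = 0.374 SD for a follow-up-only comparison. With baseline adjustment at the stated correlation of .5 it is 0.374 × √(1 − 0.25) = 0.324 SD. Two days would then imply an SD of 5.3 to 6.2 days, and one NODS point an SD of 2.7 to 3.1 points. Each is a single-test calculation at .05.

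**2. Number of tests under each reading.**
- Six months only (abstract), or one overall test per outcome: 2 tests.
- A test at each of two visits (one reading of Hypothesis 1): 2 × 2 = 4 tests.

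**3. Error if any one significant result counts.** With independent tests, family-wise error is 1 − 0.95^k:
- k = 2: 1 − 0.95² = 9.75%
- k = 4: 1 − 0.95⁴ = 18.5%

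The tests will be correlated. The article gives only the baseline to follow-up correlation, so the correlations between visits and between outcomes are assumptions. Simulating four correlated normal test statistics (2 million draws, two-sided .05 each) gives the correlated rows below; the first row follows from the formulas.

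| Correlation: visits / outcomes | Four tests, either direction | Four tests, favouring G + MH | Two six-month tests, either direction |
|---|---|---|---|
| 0 / 0 | 18.5% | 9.6% | 9.75% |
| .5 / .3 | 16.9% | 8.5% | 9.5% |
| .5 / .5 | 16.1% | 8.1% | 9.1% |
| .7 / .7 | 13.7% | 6.8% | 8.3% |

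The favourable direction matters because Hypothesis 1 predicts less gambling under G + MH. For two independent tests that rate is 1 − 0.975² = 4.9%. At correlation .7 it is about half of 8.3%, a little over 4%. A single two-sided test gives 2.5%.

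**4. Error and power if all results must be significant.** Error is at most 5%. Joint power falls: if each test has power .80 and the tests are independent, it is 0.80² = .64 for two and 0.80⁴ = .41 for four. Positive correlation raises these values. Power analysis reports no joint power.

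**5. Effect of the remedy.** Holm tests the smaller p-value first at .025. The detectable difference at that step grows by (2.241 + 0.842)/(1.960 + 0.842) = 1.10. Family-wise error is at most .05 whatever the correlation.

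**The case against.** A reader might infer that Hypothesis 1 carries a 14-19% false-positive risk, about three times the nominal .05. The documents do not support that as a plain statement:
- Separate analyses per outcome means two analyses. A repeated measures model may give one treatment test each. Power claimed for gambling days at both follow-ups makes visit-by-visit testing possible, but does not state it.
- Nowhere does the article say that one significant result would suffice. Hypothesis 1 names both follow-ups, and read literally it could require both.
- Errors against G + MH could not confirm a directional hypothesis, so the favourable-direction rate is the relevant one.
- The upper end requires independent tests, which is implausible for related measures repeated in the same people.

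These points stand, and they limit the size of the problem.

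It can also be said that multiplicity rules commonly sit in an analysis plan, which is not shown here. That stands too: the absence of an adjustment is not by itself the finding. It does not dispose of the time-point conflict, which lies within the article. The six months in the abstract is contained in the three and six months of the hypotheses, but a claim at one visit and a claim at two are different hypotheses with different error and power.

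**Conclusion.** The point holds in a conditional form. The abstract, the hypotheses and the power section disagree on when Hypothesis 1 is judged, and two unranked primary outcomes are analysed separately against a single alpha that appears only as a power input.

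The size depends on which passage governs and on the success rule. If any one result suffices, two-sided error is about 8-10% (two tests) or about 14-19% (four tests); in the predicted direction it is about 4-5% or 7-10%. If all must succeed, error is controlled but .80 is not the power for Hypothesis 1. These ranges rest on two-sided tests at .05 each and on assumed correlations of 0 to .7. The time-point conflict rests on no assumption.

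**What to change.** 1. Name six months as the primary time point in the abstract, in Hypothesis 1 and in the power section, and make the three-month contrasts secondary.
2. Test NODS and gambling days at six months with Holm at family-wise .05, or in a fixed sequence chosen in advance.
3. State that Hypothesis 1 is supported if at least one outcome is significant under that procedure, and that the claim extends only to that outcome.

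**Cost.** The text changes are small, and three-month results no longer count as confirmation. Holm's first step raises the detectable difference by about 10%. Keeping .80 power at that step would instead need 1.10² ≈ 1.21 times as many followed participants. A fixed sequence avoids this for the outcome tested first, but the second can be claimed only if the first succeeds.

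The 10% should not be applied to the published two days and one point as if those belonged to Hypothesis 1. They are tied to the whole sample, whereas Hypothesis 1 concerns the roughly 50% expected under Inclusion criteria to have co-occurring symptoms. If it is tested in that half alone, with the same SD and attrition, the starting values are √2 times larger: about 2.8 days and 1.4 points, rising to about 3.1 and 1.6 at Holm's first step.

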## Abstract

**Background:**

Comorbidity between problem gambling and depression or anxiety is common. Further, the treatment needs of people with co-occurring gambling and mental health symptoms may be different from those of problem gamblers who do not have a co-occurring mental health concern. The current randomized controlled trial (RCT) will evaluate whether there is a benefit to providing access to mental health Internet interventions (G + MH intervention) in addition to an Internet intervention for problem gambling (G-only intervention) in participants with gambling problems who do or do not have co-occurring mental health symptoms.

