### Baseline assessment

The online assessment includes a demographic profile (age, gender, education, marital status, income, employment status) and a gambling, mental health and treatment history assessment. Problem gambling severity will be measured using the past year PGSI and the past three month version of the NORC DSM-IV Screen for Gambling Problems (NODS) which indicates DSM-IV severity [39, 40]. Hodgins [41] administered the NODS to problem gamblers as part of a 1-year follow-up after a brief treatment to assess its utility as a treatment outcome measure. Internal reliability was fair to good and the factor structure and item-total correlations supported the existence of a single higher order construct that correlated moderately with gambling behaviour and outcome. Prior treatment access will be measured using the items developed for previous trials conducted by Hodgins et al. [33, 34]. In addition, participants will be asked to identify a treatment goal (quit or reduced gambling) and how successful they think they will be (0 “not at all” to 10 “extremely”) in the next three months and in the next six months.

Severity of depressive symptoms will be measured using the PHQ-9 [42]. Severity of anxiety symptoms will be measured using the GAD-7 [43]. The Kessler 10 (K10) questionnaire will be included to provide a continuous measure of general psychological distress that is responsive to change over time. The K10 has been well validated and its brevity and simple response format are attractive features. It also produces a summary measure indicating probability of currently experiencing an anxiety or depressive disorder [29, 30].

Hazardous alcohol consumption will be measured using the Alcohol Use Disorder Identification Test Consumption measure (AUDIT-C) [44]. Illicit drug use will be assessed in a manor commonly used on general population surveys – by asking if the participant had used (from a list) any of the primary illicit drug categories ever, and in the last 12 months [45]. A more detailed assessment of illicit drug use is not warranted in this situation as the incidence of use will be too low for detailed analysis.

Quality of life will be assessed by the WHOQoL-8, an eight-item version of a widely used measure. This short form has been used in a number of countries, is robust psychometrically, and overall performance is strongly correlated with scores from the original WHOQoL [46].

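### Hypotheses 1 and 2 together predict an effect that differs by mental health status, but no condition-by-K10 interaction is named to test that difference

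*Protocol article*

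**What the plan says.** The Abstract and the Major research questions section of the protocol article set out a contrast. In gamblers with co-occurring symptoms, G + MH is predicted to give significantly better gambling outcomes than G-only (Hypothesis 1). In gamblers without such symptoms, the two websites are predicted not to differ significantly (Hypothesis 2). The Abstract gives the motive, contrasting gamblers with and without such symptoms: "the treatment needs of people with co-occurring gambling and mental health symptoms may be different from those of problem gamblers who do not". Inclusion criteria defines the two groups by K10, with 22 as the cut-off, and expects about half the sample in each.

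On analysis, the Data analysis section states: "Analyses for Hypotheses 1 and 2, comparing outcomes between groups, will employ mixed effects repeated measures models". It then adds: "This same analytic approach, with the addition of interaction terms, will be used for secondary analyses examining moderators (e.g., extent of use, gender"). The Background describes these moderators as acting on the benefit of G + MH among gamblers who already have co-occurring symptoms.

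The Power analysis section refers to a difference between conditions, without saying whether this is in the whole sample or in one K10 group: "This sample size will be sufficient to detect a difference of about two gambling days per month between conditions at each follow-up interval". It makes a matching claim for the NODS: "this sample size will be sufficiently powered to detect a 1 point difference on the NODS at six months".

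**The concern.** The two hypotheses are worded as a significance result in one group and a non-significance result in the other. Read side by side, they invite the conclusion that mental health status changes the effect of adding the mental health website. That conclusion needs a comparison of the two effects, and none is named. A p-value below .05 in one group and above .05 in the other can easily arise when the true effects are equal, because each group has only part of the sample and each test can miss.

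Hypothesis 2 adds to the problem. A non-significant result in about 56 followed participants per arm counts as agreement with the prediction, so low power works in its favour. No margin is given that would turn non-significance into evidence of a negligible difference.

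The practical question is whether to offer the mental health website to all online gambling clients or only to those with symptoms. The answer depends on how far the two effects differ, and that is the quantity the described analysis does not estimate.

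**Working it through.** **Inputs from the Power analysis section**
- "assuming a correlation of .5 between baseline and follow-up values, power = .80 and an α = .05".
- 280 randomised; "we estimate that we will successfully follow about 224 participants at six months (20 % attrition"). Check: 280 x 0.80 = 224, which reproduces.
- Target differences: 2 gambling days per month, or 1 NODS point.

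**Input from Inclusion criteria**
- About 50% with K10 of 22 or more, so 112 followed per K10 group.

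**Assumptions (not in the article)**
- 1:1 allocation, giving 56 followed per arm within each K10 group; two-sided test; the same SD in both groups; one outcome at one follow-up; normal approximation.
- The outcome SDs are not given, so the stated 80% power cannot be reproduced. I back-solved the SD from it under two readings.

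**Step 1. Implied SD for 2 days.** SD = 2 / [(1.960 + 0.842) x sqrt(2/n per arm)].
- Reading A, power refers to the whole sample (112 per arm): 2 / (2.802 x 0.1336) = 5.34 days.
- Reading B, power refers to one K10 group (56 per arm): 2 / (2.802 x 0.1890) = 3.78 days.

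With r = .5 a change-score analysis gives the same SDs. The percentages below depend only on the power, so they apply equally to the NODS target.

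**Step 2. Power within one K10 group.** SE = SD x sqrt(2/56); power = Phi(2/SE - 1.96).
- A: SE = 1.010; Phi(1.981 - 1.960) = 51%.
- B: SE = 0.714; Phi(2.802 - 1.960) = 80%.

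**Step 3. Chance of the predicted pattern when the true effect is 2 days in both groups.** The groups are disjoint, so the chance is p(1 - p), where p is the power from step 2.
- A: 0.508 x 0.492 = 25%.
- B: 0.80 x 0.20 = 16%.

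Simulation agrees (25.0% and 15.9%). Among trials showing the pattern in this way, an interaction test would be significant in only about 10% (A) or 13% (B).

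The figure depends on the common effect, and p(1 - p) cannot exceed 25%:

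| True effect in both groups | A | B |
|---|---|---|
| 1 day | 14% | 21% |
| 1.5 days | 22% | 25% |
| 2 days | 25% | 16% |
| 3 days | 13% | 1% |

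**Step 4. Power of the interaction when the effect is 2 days with symptoms and 0 without.** SE = SD x sqrt(4/56).
- A: SE = 1.428; Phi(1.401 - 1.960) = 29%. Smallest interaction detectable with 80% power: 2.802 x 1.428 = 4.0 days.
- B: SE = 1.010; Phi(1.981 - 1.960) = 51%. Smallest detectable: 2.802 x 1.010 = 2.8 days.

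For 80% power to detect a 2-day interaction, the followed sample would need to be 224 x (4.0/2)^2 = 896 under A, or 224 x (2.83/2)^2 = 448 under B. Dividing by 0.8 gives 1120 or 560 randomised.

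**The case against.** The strongest reply is that the article never gives the fixed effects of its models. A reader might infer that two separate subgroup models will be fitted, but no sentence says so. The separate analyses mentioned in the Data analysis section are one per outcome. The Power analysis section even hints at a joint layout: 92 women at 23 per condition gives 92/23 = 4 cells, which fits arm by mental health status. The moderator list is also only a set of examples. All of this stands, and I do not claim that separate models are planned.

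A reader might also infer that the trial means to show that G + MH helps only gamblers with symptoms. The Background does not go that far. It puts benefit in the symptomatic group first and, as a lesser aim, lack of disadvantage in the others. Hypothesis 1 is validly tested within its own group and needs no interaction.

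A third tempting inference is that K10 is used merely as a cut at 22. The Baseline assessment section says it is included "to provide a continuous measure of general psychological distress that is responsive to change over time", so only the group definition is a split. A continuous interaction would be more powerful only if the moderation is close to linear.

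What the reply does not remove is the wording that is present. The hypotheses state the criterion as significant here and not significant there. The article describes the analysis of Hypotheses 1 and 2 as a group comparison, and introduces interaction terms as an addition for secondary analyses. The Background places those moderators inside the symptomatic group. An analysis plan that followed this text would have no test of the predicted contrast, so this is more than detail left out of a condensed article.

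**Conclusion.** The point holds in a limited form. The test of Hypothesis 1 is sound in itself. What is not supported is any conclusion that the effect differs by mental health status, or that there is no difference in the group without symptoms, drawn from the two significance results. At the planned effect size, equal true effects would produce the predicted pattern in about 16% to 25% of trials, depending on whether the stated power applies to each K10 group or to the whole sample. The article does not say which.

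These percentages rest on the assumptions listed in the working. They do not cover the joint pattern over two primary outcomes and two follow-ups, and they would be much smaller if the common effect were well above the planned one. K10 status is not a stratification factor, so 56 per arm within each group is an expectation only.

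**What to change.** In the Data analysis section, state the following:
- For each primary outcome, one mixed model is fitted to all randomised participants with condition x time x baseline K10 status (22 or more versus below).
- Hypotheses 1 and 2 are contrasts from that model, each reported with a 95% CI.
- Any statement that the benefit differs by mental health status rests on the condition-by-K10 estimate at six months with its 95% CI, and not on comparing the two p-values.
- Non-significance in the group without symptoms is not reported as evidence of no difference; the CI shows which differences remain compatible with the data.

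The same interaction with K10 as a continuous variable may be added as a sensitivity analysis.

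The cost is analysis wording only, since K10 is part of the baseline survey completed before randomisation. The downside is precision: at 224 followed, the interaction has about 29% to 51% power for an effect confined to the symptomatic group. The plan should say so in advance and accept that the differential conclusion may have to be softened.
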